This single-blind randomised mechanistic controlled trial therefore uses CTS as a model system to investigate the mechanisms of action of a 6-week progressive home-based neurodynamic exercise intervention on nerve function, structure and neuroinflammation in patients with CTS compared to a positive control intervention (steroid injection) and a negative control intervention (advice). We will also include a healthy control group who will provide normative data on nerve structure, function, and inflammatory markers. The deep and comprehensive phenotyping of our patient cohort includes different advanced neuroimaging sequences (i.e., diffusion, T2 mapping and anatomical images with magnetisation transfer preparation) that combined with our functional (i.e., quantitative sensory testing, nerve conduction studies, serum protein levels in blood) could help disentangle the mechanisms of action of neurodynamic exercises locally. In future analyses, we will explore whether these neurodynamic exercises have an effect proximally at the level of the dorsal root ganglia (DRG).

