### Assignment of interventions and blinding

Patients will be randomly assigned to one of three interventions after their first baseline appointment. Assignment will be randomised and stratified by electrodiagnostic test severity (mild/moderate) using an online tool (https://www.randomizer.org) and implemented in REDcap. The allocation ratio will be 1:1:1. The examiner performing the outcome measures will be blinded. The central research team, including the statistician, will also be blinded.

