#### Steroid injections

Steroid injections are routine first-line treatment for patients with CTS [37] and will be used as a positive control group as they have established short term benefits [38, 39] and change nerve structure [40]. Patients in this group will receive a single injection of 40 mg depomedrone suspended in polyethylene glycol into the carpal tunnel (extraneurally) using the landmark technique [41]. Briefly, the needle will be inserted into the proximal carpal tunnel at the distal wrist crease immediately ulnar to the palmaris longus tendon [41]. A trained medical doctor will perform this technique as per standard practice at OUH NHS Trust. Participants will receive an information leaflet, and will be instructed to keep performing their usual activities but not start any new treatments during the 6 weeks of the study intervention (Suppl. Information Appendix B).

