### Sample size calculation

Sample size is based on our previous MRI study demonstrating intraneural signal reduction after neurodynamic exercises [25]. Conservatively assuming a 30% smaller effect size (within subjects repeated measures ANOVA with 3 groups & 2 time points), *n* = 63 patients are required (*n* = 21 per group, d = 0.22, power = 80%, alpha = 0.05). To account for a 20% drop out rate, we will include 78 participants (26 per group). We will include 30 healthy participants to establish normative data.

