### Statistical analysis

Data will be analysed using R Studio (v 7.2, RStudio, Boston, USA) [58]. The distribution of the data will be checked for normality, and parametric, or non-parametric methods will be used as appropriate. Participants’ characteristics in each group will be described at baseline.

Two-way repeated measures ANCOVAs (factors time and intervention, adjusted for baseline measurements as a continuous covariate) followed by post-hoc testing will be performed to identify differences in primary/secondary outcome measures among groups and over time. If there is deviation from normality, we will use non-parametric alternatives (i.e. ranked ANCOVA).

If the missing values mechanism is likely to be missing at random (MAR) or missing completely at random (MCAR), we will perform multiple imputation by chained equations. The appropriate model will be fitted in all the completed datasets, then coefficient estimates and standard errors will be pooled across imputations using Rubin’s rules.

The level of statistical significance will be set at *p* = 0.05. Adjustments for multiple comparisons will be used as appropriate.

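### The three-arm by two-time test that is powered and stated for fractional anisotropy can reject through the steroid arm alone, so it does not by itself test the exercises; exercise minus advice should be the named primary contrast

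*Protocol article*

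**What the plan says.** The Background of the protocol article gives the aim as the mechanisms of action of the home exercise programme, "compared to a positive control intervention (steroid injection) and a negative control intervention (advice"). Under Steroid injections, that arm "will be used as a positive control group as they have established short term benefits [38, 39] and change nerve structure [40"]. Nerve structure is the domain of the primary outcome, FA of the median nerve at the wrist.

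The Sample size calculation section describes the powered test as "within subjects repeated measures ANOVA with 3 groups & 2 time points" and states that 63 "patients are required (*n* = 21 per group, d = 0.22, power = 80%, alpha = 0.05"). It names neither an ANOVA term nor a pairwise comparison.

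The Statistical analysis section specifies the model as "Two-way repeated measures ANCOVAs (factors time and intervention, adjusted for baseline measurements as a continuous covariate"). The same sentence then gives the next step and the purpose of the analysis: "followed by post-hoc testing will be performed to identify differences in primary/secondary outcome measures among groups and over time". On multiplicity it says "Adjustments for multiple comparisons will be used as appropriate". The post-hoc comparisons are not listed or ranked.

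**The concern.** The trial asks whether the exercises act on the nerve. The comparison that isolates this is exercise against advice, the negative control. The stated test has other nulls:

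- **Group effect and group-by-time interaction:** all three arms are equal. This is false as soon as steroid differs from advice, which is the reason for having a positive control.
- **Time main effect:** no average change from baseline. This is false if steroid works, and also if all arms change together, for example through natural course.

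Rejection of any of these is compatible with inert exercises. At stake is what a significant primary test means, and what the 80% power describes. A reader would naturally take it as the chance of detecting an exercise effect.

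**Working it through.** **Inputs from the document.** Three arms at 1:1:1, FA at baseline and 6 weeks, 21 evaluable per arm (26 enrolled), effect 0.22, alpha 0.05, power 80%.

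**Assumptions.** The document gives no SD for FA, no correlation between baseline and 6 weeks (rho), and no expected steroid effect. Effects are therefore in SD units over a range, with rho 0.4 and 0.5.

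**1. The plan's own figure.** The stated 0.22 gives a total near 63 only if read as Cohen's f. With noncentrality lambda = f² × N × m / (1 − rho) and m = 2 time points:

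- Group-by-time (2 and N − 3 df): N = 63 results if rho is 0.40 to 0.42. At rho 0.4, lambda = 0.0484 × 63 × 2 / 0.6 = 10.16.
- Time (1 and N − 3 df): N = 63 results if rho is 0.25 to 0.28.
- At rho 0.5 the two terms need 54 and 45.

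So 63 is attainable, but the text does not show which term was powered. Dropout: 63 / 0.8 = 78.75, or 79 against the stated 78, which is immaterial.

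**2. What f = 0.22 means for one arm.** If one arm differs from two equal arms by D, then lambda = n × (2/3) × D² / (2(1 − rho)). With n = 21 and rho 0.4, D = √(10.16 / 11.67) = 0.93 SD.

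**3. Rejection rates when exercise equals advice.** 20,000 simulated trials per scenario, bivariate normal outcomes, rho 0.4, 21 per arm (26 in brackets). Interaction and time are from the repeated-measures ANOVA; group and contrast are baseline-adjusted.

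| True situation | Interaction | Group | Time | Exercise − advice |
|---|---|---|---|---|
| Steroid 0.3 SD only | 13% (15%) | 16% (20%) | 11% (13%) | 5% |
| Steroid 0.5 SD only | 30% (37%) | 41% (49%) | 22% (26%) | 5% |
| Steroid 0.8 SD only | 66% (76%) | 81% (89%) | 48% (56%) | 5% |
| Steroid 0.93 SD only | 80% (89%) | 92% (97%) | 60% (70%) | 5% |
| All arms change 0.2 SD | 5% | 5% | 30% (36%) | 5% |
| All arms change 0.3 SD | 5% | 5% | 57% (66%) | 5% |
| All arms change 0.5 SD | 5% | 5% | 95% (98%) | 5% |

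With no effect anywhere, every ungated test rejects in about 5%. At rho 0.5, steroid effects of 0.5, 0.8 and 1.0 SD give 44%, 86% and 97% for the group test.

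In the fourth row the steroid arm alone delivers the full planned 80% on the interaction while the exercises do nothing.

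**4. Power of the direct contrast.** The standard error is √(1 − rho²) × √(2/n). At n = 21 and rho 0.4 this is 0.917 × 0.309 = 0.283 SD. By normal approximation, power is 42% at 0.5 SD, 81% at 0.8 SD and 91% at 0.93 SD. The difference detectable with 80% power is (1.96 + 0.84) × 0.283 = 0.79 SD. At rho 0.5 it is 2.80 × 0.866 × 0.309 = 0.75 SD.

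**5. Cost of the omnibus gate.** Rho 0.5, 21 per arm, exercise 0.8 SD above advice:

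- Steroid at 0.4 SD: 84% ungated, 74% if the omnibus must be significant first, and 70% if Bonferroni over three pairs is added. A second run gave 82%, 72% and 68%.
- Steroid at 0 or 0.8 SD: 83% ungated and 79% gated.

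The gate costs about 4 to 10 percentage points before any Bonferroni step.

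**The case against.** The strongest reply is that the plan does not stop at the omnibus test. When steroid works, rejecting equality of three arms is correct, and post-hoc comparisons then locate the difference. The exercise-advice comparison keeps about 5% error in every scenario above. With three arms and only steroid different, just one pairwise null is true, so the gated sequence also protects the familywise error. All of this stands.

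A reader might infer more than the documents support:

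- **That the plan will credit the exercises with an effect on a significant omnibus or time result.** No section says so, and the Abstract presents the two control arms as aids to interpretation.
- **That exercise versus advice has no power.** It has about 91% at the 0.93 SD implied by the planning effect (rho 0.4). With exercise at 0.4 SD and steroid at 0.8 SD, the omnibus has 74% and the gated contrast about 30%, but most of that gap comes from the small assumed exercise effect.
- **That a common change spoils the whole analysis.** It affects only the time term. The wording on differences among groups and over time can also be read as the interaction, which is immune. The time rates come from the repeated-measures ANOVA in the sample-size section and need not carry over exactly to the ANCOVA. The document does not show that a common change in FA is likely: the most affected hand is chosen only in bilateral cases, and not on FA.

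A separate analysis plan may rank the contrasts, so their absence from an article is not the point. The point is that the test the article does state and power is aimed at a different null from its aim. Since the aim names both controls, exercise versus steroid also remains a legitimate comparison.

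**Conclusion.** The concern holds in a limited form. The group and interaction tests are expected to reject through the positive control alone, and a time main effect can also reject under a shared change, so none can by itself show an exercise effect. The 80% belongs to a three-arm ANOVA with an unnamed term, not to exercise versus advice. Because the right contrast is available post hoc at correct error, the result is a misdirected and less powerful primary test rather than a certain false conclusion. The mismatch of nulls needs no numerical assumption. The sizes (41% to 81% group rejection for steroid effects of 0.5 to 0.8 SD; roughly 4 to 10 points of power lost to the gate) rest on assumed SD-unit effects, rho 0.4 or 0.5, normality and 21 per arm. It should be corrected, but it does not threaten the trial's conduct.

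**What to change.** In Statistical analysis, pre-specify exercise minus advice in 6-week FA, from the baseline-adjusted three-arm model, as the primary contrast at two-sided 0.05, not conditional on the omnibus F. Use steroid minus advice as the check that FA responds to an active treatment, and keep exercise minus steroid as secondary. State that a time main effect will not be taken as evidence for the exercises.

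In Sample size calculation, say that the 80% refers to the three-arm ANOVA and name the term. Add the detectable exercise-advice difference for 21 per arm: about 0.8 SD for roughly 80% power if rho is 0.4 to 0.5, with rho stated as an assumption.

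The cost is wording in the analysis plan and registry before unblinding, by the amendment route that the Ethics and dissemination section already describes. No new patients or data are needed. The small downside is that an omnibus or time effect can no longer be presented as the primary positive result.

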### Primary mechanistic outcome measure

#### Magnetic resonance neurography (MRN): Fractional Anisotropy (FA)

All participants will attend a MRN session on a 3 Tesla MAGNETOM Prisma scanner (Siemens, Germany) to visualise the median nerve at the wrist using a dedicated 16-channel wrist coil (Siemens, Germany).

Participants will be positioned in a ‘superman’ position, lying prone with the wrist above their head resting in the centre of the bore. The protocol includes the acquisition of multishell (b = 0, b = 300 and 800 s/mm^2^) diffusion-weighted imaging scans. In addition, true fast imaging with steady-state free precession (TRUFI) with/without magnetisation transfer (MT) preparation, and T2-mapping scanning will be acquired (see other markers in MRN). Scan parameters are summarised in Table 1.

**Table 1 Tab1:** MRI sequence parameters at the wrist

	3D TRUFI	T2 mapping	Diffusion Weighted Imaging (DWI)
Repetition time (TR)	10.1 ms	7,110 ms	4,000 ms
Echo time (TE)	4.14 ms	14.7–147 ms	47 ms
Flip angle (FA)	20°	Variable	90° and 180°
Field of view (FoV)	74.3 mm	225 mm	160 mm
Dimensionality	3D	2D	2D
Slice thickness	0.6 mm	1 mm	1 mm
Number of slices	176	50	50
In-plane resolution	0.1 × 0.1 mm	0.5 × 0.5 mm	1 × 1 mm
Echo spacing	N/A	N/A	0.96ms
Fat suppression	No fat saturation	Fat saturation	Fat saturation
Parallel acquisition technique	GRAPPA factor 2	GRAPPA factor 2	GRAPPA factor 2
Bandwidth	350 Hz/Px	132 Hz/Px	1220 Hz/Px
b values	N/A	N/A	0 (NSA = 8), 300 (NSA = 5), 800 (NSA = 8)
No. signal averages	1	1	8 (b = 0), 5 (b = 300), 8(b = 800)
Scan time single phase-encode blip (right-left or left-right)	N/A	N/A	6.42, 7.42
Total scan time (min)	10.16	10.32	14.18

N/A: not applicable; NSA: number of signal averages

All diffusion image pre-processing will be performed using the FMRIB Software Library (FSL) Diffusion Toolbox v 6.0 (Oxford, UK). Briefly, TOPUP [42, 43] and EDDY [44] tools will be applied to correct for distortions and eddy currents followed by DTIFIT [45] to compute the diffusion tensor model. FLIRT will be used to co-register the diffusion metrics to the anatomical sequences.

Median nerve region of interests will be determined at three levels: the distal radio-ulnar joint (proximal), pisiform (mid-carpal tunnel) and hook of hamate (distal carpal tunnel). Fractional anisotropy (no units) will be computed as our primary outcome measure.

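### A normality check on the data, not on the model residuals, decides whether the primary FA analysis is in FA units or in ranks, so an FA-unit effect with its confidence interval is not guaranteed

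*Protocol article*

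**What the plan says.** The primary outcome is continuous: "Fractional anisotropy (no units) will be computed as our primary outcome measure" (section on magnetic resonance neurography). The Statistical analysis section opens with a general rule: "The distribution of the data will be checked for normality, and parametric, or non-parametric methods will be used as appropriate". It then gives the main model, "Two-way repeated measures ANCOVAs (factors time and intervention, adjusted for baseline measurements as a continuous covariate"), whose purpose is "to identify differences in primary/secondary outcome measures among groups and over time". The next sentence applies the rule to that model: "If there is deviation from normality, we will use non-parametric alternatives (i.e. ranked ANCOVA"). The rule therefore covers the primary outcome.

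The only object named for checking is the data. The section does not mention residuals, and it does not say that an FA-unit estimate is kept if the ranked model is used.

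**The concern.** The normality assumption of ANCOVA concerns the errors once baseline and arm are in the model. It does not concern the raw distribution of baseline or 6-week FA. If baseline FA is skewed, raw values at both visits can look non-normal while the errors are normal and the ANCOVA is fully valid. A check on the data can then discard a sound analysis.

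What is at stake is the form of the primary result. The planned model gives an adjusted difference in FA between arms, which can be read against the normative data that the healthy group is recruited to provide. Ranked ANCOVA gives a difference in mean ranks among the patients, which cannot. Which of the two is reported would be settled only after the outcome data are seen.

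**Working it through.** The plan gives no figure of its own on this point, so there is none to reproduce. The check asks how often each kind of normality check would abandon a model that is exactly right.

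**Inputs from the protocol.** There are three arms and 63 evaluable patients, so 63/3 = 21 per arm (Sample size calculation). FA is measured at baseline and 6 weeks, and baseline is the covariate. The model therefore has one follow-up value per patient.

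**Assumptions not in the protocol.** The check is Shapiro-Wilk at 5%. Mean FA is 0.45, baseline SD 0.05, slope of 6-week on baseline FA 0.7, and error SD 0.03. For power, two arms are shifted by 0.03. Errors are exactly normal throughout. Baseline is either normal or left-skewed (skew-normal, shape -6, same mean and SD). Each setting has 3,000 simulated trials, so the Monte Carlo standard error of a 5% rate is sqrt(0.05 × 0.95/3000) = 0.4 points.

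**Step 1, by formula.** With exactly normal data, a check that fails if any of the 3 × 2 = 6 arm-by-time cells fails at 5% has probability 1 − 0.95^6 = 0.265, taking the cells as independent. A single pooled check has probability 0.05.

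**Step 2, by simulation.** Share of trials sent to ranks although the model is valid:

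| What is checked | Normal baseline | Left-skewed baseline |
|---|---|---|
| Model residuals | 4.9–5.5% | 4.9–5.4% |
| 6-week FA, arms pooled | about 5% | 17–19% |
| Baseline or 6-week FA, each pooled | 9% | 85–86% |
| Any of 6 arm-by-time cells | 25% | 74% |

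The 25% agrees with the 26.5% from the formula.

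**Step 3, why the skew matters.** Since 6-week FA = constant + 0.7 × baseline + error, baseline shape passes into the raw follow-up values. Here 0.7 × 0.05 = 0.035, and the within-arm SD at 6 weeks is sqrt(0.035² + 0.03²) = 0.046. Follow-up skewness is then (0.035/0.046)³, or about 0.44, of the baseline skewness. This is why pooled 6-week values switch less often than checks that include baseline. The residuals carry none of it.

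**Step 4, error rates.** Here the switching rule was run on the six-cell check and on the check of pooled baseline or pooled 6-week values.

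| | Normal baseline | Left-skewed baseline |
|---|---|---|
| Type I error: ANCOVA | 4.7% | 4.6% |
| Type I error: always ranked | 5.0% | 5.1% |
| Type I error: switching rule | 4.8–4.9% | 5.0–5.1% |
| Power: ANCOVA | 91.4% | 91.7% |
| Power: always ranked | 86.8% | 86.3% |
| Power: switching rule | 90.2–91.1% | 86.9–87.7% |

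The switching rule costs 91.4 − 91.1 = 0.3 to 91.4 − 90.2 = 1.2 points with a normal baseline, and 91.7 − 87.7 = 4.0 to 91.7 − 86.9 = 4.8 points with a skewed one. Other simulated settings without skew gave 0.5 to 2 points.

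**The case against.** The strongest reply has four parts.

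- **The wording may be loose.** The sentence that triggers ranked ANCOVA follows the ANCOVA sentence directly and does not say what is checked, so residuals may be meant. This cannot be excluded. But the data are the only object that the section names, and on either reading the scale of the primary result waits on a check made after the data are in.
- **No test, threshold or cell-wise rule is stated.** The wording also allows plots and judgement, and an analysis plan that is not shown may settle it. This stands: every switching rate above is conditional on an assumed procedure. The missing test is not the point, though. The point is the rule that the article does state.
- **The statistical harm is small.** This stands. Type I error holds, and the average power cost is about a point or two unless baseline is skewed.
- **A rank test does not forbid reporting FA means or differences beside it.** This also stands. The FA-unit result is not guaranteed, which is weaker than saying that it will be lost.

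A reader might also infer some stronger points that the documents do not support.

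- **Severity mix as the cause.** Randomisation is stratified ("Assignment will be randomised and stratified by electrodiagnostic test severity (mild/moderate"), so one might blame the mixing of mild and moderate cases. In a separate simulation (21 per arm, correlation 0.6, 2,000 trials), strata 0, 1, 1.5 and 2 SD apart gave pooled 6-week switching of 4.8%, 4.8%, 4.0% and 6.7%. The six-cell check gave 28%, 25%, 21% and 22%, so mixing added no excess. The protocol divides the two grades at a motor latency of 4.5 ms on a continuous scale, and it gives no FA figures that suggest widely separated groups.
- **A treatment effect as the cause.** Shifting two arms by 0.7 or 1.0 SD gave pooled switching of 5.0% and 4.4%.
- **Accumulation over nerve levels.** The section on magnetic resonance neurography says "Median nerve region of interests will be determined at three levels". Multiplying trigger rates over them would need independence, but the values come from the same nerve.
- **Failure of multiple imputation.** Completed datasets have the same size, so ranks span the same range in each. No error in pooling rank coefficients has been shown.

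**Conclusion.** The point holds, at minor-to-moderate severity. As written, a check on the distribution of the data chooses between FA units and ranks for the primary outcome, and it can replace a valid ANCOVA. Under an assumed Shapiro-Wilk test at 5%, a residual check would do so in about 5% of trials. A data check would do so in about 5% to 26% with exactly normal data, and in 17% to 86% in the skewed-baseline example, depending on what is checked. The direction is firm. The rates rest on an assumed test and assumed FA distributions, because the protocol gives neither.

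The consequence is a primary result whose scale depends on the outcome data, without an assured FA-unit effect and confidence interval. A reader might go further and infer false-positive findings or a badly underpowered trial. The calculations support neither.

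**What to change.** State that 6-week FA will be analysed by baseline-adjusted ANCOVA in FA units whatever a normality check shows, with adjusted mean differences between arms and 95% confidence intervals. Base model checking on residuals, not raw values. If residuals look poor, keep the FA-unit estimate and use robust standard errors, a bootstrap interval or a permutation p-value. Report ranked ANCOVA as a sensitivity analysis only.

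The cost is a change of wording in the protocol or analysis plan, with no extra data or patients. The one downside is that, if residuals are truly heavy-tailed, the rank test would have been somewhat more powerful as the primary test. It would still be reported.
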